### Setting

The WHC is being rolled-out sequentially in four HTC/healthcare clinics and four outpatient substance use rehab centers located in selected disadvantaged communities (townships) in Cape Town. These sites were identified and approved by the City of Cape Town Health Department. Each HTC/healthcare clinic was paired with a substance use rehab center based on geographic proximity, and each pair was randomized by computer into four succeeding 6-month implementation cycles where implementation of the WHC is taking place simultaneously at the paired sites.

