HIV testing is not part of the research because it is performed by clinic staff as part of standard clinic operations. As proof of HIV-positive status, participants must provide a clinic-issued document such as an antiretroviral (ARV) card or ARV medication with identifiable data linking to the participant, or they must consent the research staff to access their hospital records for their results. Viral load is also collected at baseline and 6-month follow-up from the South African National Health Laboratory Service (NHLS) database in the clinics. Viral load testing is also part of the standard of care and the clinics routinely perform HIV viral load testing 6 months after a patient begins taking ART and then 12 months later; however, these intervals may vary by clinic. Viral load test information will be used to validate self-reported ART adherence.

In each cycle, the objective is to enroll 120 women (60 from a HTC/healthcare clinic and 60 from a substance use rehab center) for a sample total of 480, and to follow each enrolled participant at 6 months, with an expected follow-up rate of 90%. At the end of the 6-month follow-up period, we will assess effectiveness of the program using pre-post comparisons to determine whether women reduced their AOD use, are adhering to their ARV regimen, have reduced their sex risk behaviors (e.g., using a condom at every sex act; less transactional sex), and have experienced less to GBV. At the end of each cycle, we will conduct FGDs with a subsample of women who participated in both workshops of the intervention and completed their 6-month follow-up appointment. These study activities will enhance our understanding of women’s satisfaction with the WHC program and suggest modifications to the program for broader acceptability and implementation that will be incorporated into the next cycle.

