### Analysis

The analysis will treat count outcomes as Poisson distributed. A number of multilevel factors can impact the outcomes, including site/clinics, city, time, and the type of the site (HTC vs. substance use rehab). Because individuals are clustered within sites and sites are clustered within a city, we need to consider the variance inflation factor that results in this clustering. We considered a number of approaches: using random effects, fixed effects, or Generalized Estimating Equations (GEE) considering population-averaged methods. Although a random effects model for sites seems a natural approach, we needed to consider fixed effects of the city and of the site type, which would leave little power left to estimate the random effects distribution. Consequently, we will also use two other methods, GEE and the fixed effects model, to assess sensitivity by comparing the results across these models.

We will use Stata Release 14 (College Station, TX) and SAS version 9.2 (Cary, NC). Data will be examined to determine the extent to which they meet appropriate distributional assumptions. We will use methods described by Ecob and Der to identify outliers in longitudinal models and use methods of case downweighting when extreme cases are identified [40]. Missing data will be handled using multiple imputation methods [41]. The patient-level analyses will be organized into three groups to examine (a) successful reduction of risk behaviors targeted by the WHC (i.e., effectiveness), (b) patient satisfaction, and (c) increasing the number of women receiving ART and adhering to ART, and being admitted to substance use rehab.

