To assess effectiveness, the analysis will compare changes from baseline to 6-month follow-up on the amount of alcohol consumption, biological and self-reported drug use, condom use at last sex, number of sex partners over the past 6 months, and values from scales that measure relationship power and communication. We will start with descriptive analyses, including measures of central tendency, and dispersion (e.g., means, medians, proportions, standard deviations). Bivariate analysis will include paired t-tests, Wilcoxon rank-sum, and tabular statistics and the chi-square test. For multivariable analysis, the xtlogit and xtgee function will be used to specify random effects or fixed effects, and will assume that the correlation matrix is exchangeable. The models will control for other covariates identified in bivariate analyses or hypothesized a priori (e.g., condom use is correlated with substance use). One of the most important covariates in the model will be measures of patient satisfaction. Model performance and fit will be assessed with incremental elimination of variables, likelihood ratio tests, and changes in the Akaike information criterion (AIC) and Bayesian information criterion (BIC) values.

Patient satisfaction analyses will be predominately descriptive to determine if satisfaction improves with each cycle, varies by type of clinic, and by participant characteristics (e.g., alcohol use, pregnancy status).

We assume that the prevalence of patients receiving or adhering to ART or receiving treatment for substance abuse are Poisson distributed and increase from baseline to follow-up. We will use a similar approach outlined in the effectiveness analysis for bivariate and multivariable analyses. Variables considered for multivariable analysis will include patient characteristics, measures of patient success with the WHC, patient satisfaction, and clinic-level characteristics (e.g., type of clinic, provider satisfaction).

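### The rehab outcome is worded in two ways and tested as a pooled rise, though half the women come from rehab centers and those already in treatment cannot add to a rise

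*Protocol article*

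**What the plan says.** All references are to the protocol article.

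- **Sites and enrolment.** Setting lists "four HTC/healthcare clinics and four outpatient substance use rehab centers", paired by proximity. Patient-level process and data collection plans, per cycle, "60 from a HTC/healthcare clinic and 60 from a substance use rehab center", "for a sample total of 480". None of the seven eligibility criteria concerns current substance use treatment.
- **Outcome as admission.** Analysis sets three groups of patient-level analyses. The third is "increasing the number of women receiving ART and adhering to ART, and being admitted to substance use rehab".
- **Outcome as prevalence.** Later in Analysis, the prevalence of patients on or adhering to ART or "receiving treatment for substance abuse are Poisson distributed and increase from baseline to follow-up" is the stated assumption. The bivariate and multivariable methods are to resemble those of the effectiveness analysis.
- **Site type.** Analysis mentions it as a fixed effect in the general model and as one candidate clinic-level covariate for this outcome group. No interaction with time is stated, and no split by treatment status at baseline.

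**The concern.** Admission to rehab is an event that can happen only to a woman who is not already there. Receiving treatment is a state, which a woman can also leave. The protocol uses both descriptions for one outcome and expects a rise, in a sample drawn half from places that deliver the treatment.

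Under the prevalence wording, a woman in treatment at both visits contributes zero to the change. One who finishes her programme before month 6 contributes minus one, so a good result counts against the WHC. Under the admission wording, a woman already in rehab is not at risk of the event and mainly dilutes the result.

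A pooled before-after figure therefore nets new entry against ordinary exit. A null or negative figure could be read as failed linkage to rehab when women who needed linkage did get it.

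**Working it through.** **Enrolment figure.** 4 cycles x 120 = 480, which reproduces the stated total. From rehab centers: 4 x 60 = 240, or 240/480 = 50%. At the expected 90% follow-up these become 432 and 216, with the share unchanged if losses are even.

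**Contribution of one woman** (1 = in treatment, 0 = not):

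- not in treatment at baseline: change is 0 or +1
- in treatment at baseline: change is 0 or -1, never +1

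**Pooled change.** Let N = 480, T = women in treatment at baseline, s = uptake by 6 months among the others, and x = share of the T women who have completed or left by then:

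change = [s(N - T) - xT] / N

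The documents give none of T, s or x. Assumptions: s = 20%, equal at both site types, and no clinic-site woman in treatment at baseline.

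| T | x | Entries | Exits | Baseline | 6 months | Change (points) |
|---|---|---|---|---|---|---|
| 0 | - | 0.20 x 480 = 96 | 0 | 0% | 20% | +20 |
| 120 | 0 | 0.20 x 360 = 72 | 0 | 25% | 40% | +15 |
| 120 | 50% | 72 | 60 | 25% | 27.5% | +2.5 |
| 240 | 0 | 0.20 x 240 = 48 | 0 | 50% | 60% | +10 |
| 240 | 20% | 48 | 48 | 50% | 50% | 0 |
| 240 | 50% | 48 | 120 | 50% | 35% | -15 |

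Uptake among women not in treatment is 20% in every row.

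**When the sign turns.** The change is negative when xT > s(N - T).

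- T = 240: x > 0.20 x 240/240 = 20%.
- T = 120: x > 0.20 x 360/120 = 60%.
- Even if every woman in treatment leaves (x = 1), reversal needs T > sN/(1 + s) = 96/1.2 = 80. With fewer than 80 women in treatment at baseline there is attenuation but no reversal.

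**Sensitivity to the gain at clinic sites.** Start clinic sites at 5% in treatment and let the gain be 5, 20 or 40 points.

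- All rehab-site women in treatment, 70% of them still there at 6 months: pooled change -12.5, -5 and +5 points.
- Half in treatment, 50% of those still there: -8.7, +2.8 and +18 points.

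**Does a site-type main effect help?** Take the last row of the table. Clinic sites go from 0% to 20% (+20) and rehab sites from 100% to 50% (-50). The average is 0.5 x 20 + 0.5 x (-50) = -15. A main effect for site type absorbs the gap in level but leaves one common time effect. In a Poisson model with terms for site type and time, and equal numbers at each visit, the time ratio is (48 + 120)/240 = 168/240 = 0.70 with or without the site-type term. A fixed-effects logit with the woman as the unit uses only women whose status changes: 48 up and 120 down, an odds ratio of 48/120 = 0.4.

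**The case against.** The strongest reply has four parts.

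1. **Recruitment site is not treatment status.** Outreach workers also recruit in surrounding communities, and the formative phase found that many of the target women were not attending health facilities. Eligibility requires at least weekly substance use in the previous 3 months. A reader might infer from "60 from a HTC/healthcare clinic and 60 from a substance use rehab center" that half the sample is in rehab at baseline; no section says so. This stands: the rows with T = 240 are the upper end, and reversal is a possibility that depends on unstated rates.
2. **The analysis set may be in an unseen document.** An article need not define the at-risk set for an outcome that is not powered. This stands as far as a missing definition goes. The point here is different: the article states an expected rise in prevalence over time, and that analysis, applied as written, has the defect.
3. **Site type is not ignored.** It is named as a factor and a candidate covariate, and an interaction with time could be added later. But nothing stated separates the changes, and the level terms that are stated do not.
4. **Linkage is measured elsewhere.** Table 1 includes linkage referrals by participant and staff report, and the percentage of women referred who seek related services. Timely service linkage is a service outcome under Aim 2. This stands, so it would go too far to say that the trial cannot answer its linkage question.

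**Conclusion.** The point holds in a limited form. The rehab outcome has two wordings that behave differently, and the before-after prevalence analysis mixes entry with exit. Women in treatment at baseline cannot raise the pooled change. It is not correct that they can only lower it, since those who stay merely dilute it.

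Attenuation follows to the extent that women start in treatment. Sign reversal applies to the prevalence wording and needs exits to outnumber entries. With 20% uptake assumed, the pooled change runs from +20 points when nobody starts in treatment to -15 when all 240 rehab-site women do and half leave. The mixed case (120 in treatment, half leaving) gives +2.5. These are illustrations, not estimates.

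Severity is moderate. The Power section concerns ART adherence and viral suppression, so the harm is confined to the rehab outcome, and separate linkage measures remain.

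**What to change.** 1. Reconcile the two wordings: state whether the outcome is entry into rehab by 6 months or being in treatment at the visit.
2. Replace the pooled before-after prevalence test with results by treatment status at baseline:
   - *Not in treatment at baseline:* the proportion newly entering rehab by 6 months, with its confidence interval. Do not test it as a change from baseline. In this group the baseline is zero by definition, so the change can only be upward.
   - *In treatment at baseline:* retention, completion and exit, shown alongside the entry result so that entries are not read alone.
3. If a pooled before-after model is kept, include a time-by-site-type term. This is a partial remedy, because rehab-site women may be a mix of those in and not in treatment.

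**Cost.** Treatment status at baseline is already needed for the planned before-after comparison, so the burden is small. The price is a smaller denominator for entry: 240 women if all rehab-site women are in treatment at baseline, or 360 if half are. At 90% follow-up these are 216 and 324. With 20% entry and clustering ignored, the 95% half-width is 1.96 x sqrt(0.2 x 0.8/216) = 5.3 points, or 1.96 x sqrt(0.2 x 0.8/324) = 4.4 points. The women left out of that denominator carry no information on uptake.

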### Patient-level process and data collection

The patient-level study includes a baseline visit and a 6-month follow-up visit to evaluate intervention effectiveness. Eligibility criteria include (1) being between the ages of 18 and 45 years, (2) self-reporting use of at least one drug, including alcohol, at least weekly during the previous 3 months, (3) reporting unprotected sex with a male partner in the past 6 months, (4) having a positive verifiable HIV test result, (5) reporting the intention to remain in the area for at least the next 6 months, (6) providing contact information, and (7) being willing to participate in alcohol and other drug screening.

A field team hired by Kheth’Impilo, the local nongovernmental implementing partner, leads the outreach and data collection activities. Trained outreach workers operate as recruiters of women within clinics and surrounding communities and track eligible women for the study, while data capturers collect patient-level data from participants at the baseline and 6-month follow-up appointments. These are well-established methods from other studies conducted in the region [34, 35]. Once participants are enrolled, clinic staff trained and certified in the WHC offer the adapted intervention to all women enrolled and to other women in their clinics who may be interested in participating, so as to operate as a real-world setting.

At each data collection visit, a member of the research/implementing team administers a face-to-face interview using a secure tablet with skip patterns and quality-control checks programmed into the interview. The study instrument includes measures of socioeconomic status, sex risk behaviors, AOD use, substance abuse treatment readiness, ART use and barriers to use, and other self-reported clinical outcomes such as TB and symptoms for sexually transmitted infections. Biological data are obtained from a urine specimen tested for pregnancy and metabolites for recent drug use. Participants also undergo a breathalyzer test for recent alcohol use. The same measures are collected at 6-month follow-up.

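### The unadjusted baseline to 6-month comparisons name two independent-sample tests (rank-sum, chi-square) for paired data, which makes that step conservative and costs power

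*Protocol article*

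**What the plan says.** The section on patient-level process and data collection describes a baseline visit and a 6-month visit for each enrolled woman. On the content of the second visit it says "The same measures are collected at 6-month follow-up", and on the purpose, "we will assess effectiveness of the program using pre-post comparisons". The target is stated as "for a sample total of 480", with the intention "to follow each enrolled participant at 6 months, with an expected follow-up rate of 90" per cent.

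In the Analysis section, the effectiveness paragraph opens by saying that "the analysis will compare changes from baseline to 6-month follow-up" for alcohol amount, drug use (biological and self-reported), condom use at last sex, number of partners, and relationship scales. After a sentence on descriptive statistics it names the unadjusted tests: "Bivariate analysis will include paired t-tests, Wilcoxon rank-sum, and tabular statistics and the chi-square test". For the multivariable step, "the xtlogit and xtgee function will be used to specify random effects or fixed effects, and will assume that the correlation matrix is exchangeable". The bivariate results are also one source of covariates for those models. A later paragraph carries a similar approach over to receipt of ART, adherence to ART, and substance abuse treatment.

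**The concern.** Baseline against 6 months is the only contrast the effectiveness paragraph has introduced when it lists the tests, and each woman supplies both values. The t-test is paired accordingly. The rank test and the categorical test beside it are not, in their standard forms, and neither the signed-rank test nor McNemar's test is named.

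Two distinct problems follow if the list is applied as written:

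- Rank-sum, or chi-square on a visit-by-outcome table, treats the two visits as separate groups of women. The within-woman correlation is ignored and the standard error of the change is misjudged.
- Chi-square on the cross-tabulation of baseline by follow-up status asks whether the two visits are associated. It does not ask whether the proportion changed.

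Alcohol amount and partner counts are likely to be skewed, and condom use at last sex and drug positivity are binary, so these outcomes are the natural candidates for the two unpaired tests. At stake is the chance that a real change goes undetected in the unadjusted results.

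**Working it through.** The plan states no figure for this step, so there is none to reproduce. The check sizes the effect of ignoring the pairing when the visits are compared as two samples.

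**Inputs from the article.** 480 women and 90% follow-up give 0.90 × 480 = 432 pairs. The baseline proportion for the binary illustration is 56%, the adherence figure in the Power section.

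**Assumed inputs.** Within-woman correlation ρ = 0.3, 0.5, 0.7; a log-scale shift of 0.15 for a skewed outcome; a rise from 56% to 62% for a binary outcome; two-sided 5% level. The article gives none of these.

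**Step 1, large-sample formula.** With equal variances, the variance of a paired difference is (1 − ρ) times the variance an unpaired test assumes. The unpaired standard error is therefore too large by 1/√(1 − ρ), and the true error rate is 2 × [1 − Φ(1.96/√(1 − ρ))].

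| ρ | SE ratio | True error rate |
|---|---|---|
| 0 | 1.00 | 5.0% |
| 0.3 | 1.20 | 1.9% |
| 0.5 | 1.41 | 0.56% |
| 0.7 | 1.83 | 0.03% |

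**Step 2, simulation of the tests themselves.** 432 pairs, 4,000 replicates, bivariate normal data with correlation ρ. These were exponentiated for the skewed outcome and cut at 56% for the binary one. Chi-square was applied to the visit-by-outcome table.

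Rejection rate with no true change:

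| ρ | Rank-sum | Signed-rank | Chi-square | McNemar |
|---|---|---|---|---|
| 0 | 5.0% | 4.7% | 5.6% | 5.5% |
| 0.3 | 1.8% | 4.6% | 2.7% | 4.6% |
| 0.5 | 0.7% | 5.2% | 1.5% | 4.9% |
| 0.7 | 0.1% | 4.9% | 0.7% | 4.8% |

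Power under the assumed changes:

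| ρ | Rank-sum | Signed-rank | Chi-square | McNemar |
|---|---|---|---|---|
| 0 | 58% | 53% | 43% | 43% |
| 0.3 | 59% | 66% | 43% | 52% |
| 0.5 | 62% | 79% | 41% | 58% |
| 0.7 | 65% | 95% | 39% | 70% |

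At ρ = 0.5 the loss is 79 − 62 = 17 points for the skewed outcome and 58 − 41 = 17 points for the binary one. At ρ = 0 there is nothing to gain from pairing.

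**Step 3, why chi-square departs less from 5% than the formula.** Here ρ applies to the underlying normal variables. Cut at 56%, these give binary correlations of about 0.19, 0.33 and 0.49. Putting those into the Step 1 formula gives 2.9%, 1.6% and 0.6%, close to the simulated 2.7%, 1.5% and 0.7%.

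**The case against.** The list of tests is open and assigns no test to any outcome or contrast. Alcohol amount could go to the paired t-test, since the Analysis section says distributions will be examined first. McNemar's test is itself a chi-square statistic on a table, and the reference to tabular statistics does not exclude it. Rank-sum and chi-square are also proper for comparisons between women, such as clinic against rehab or the screening of covariates, which is a second use of the bivariate step. This part stands, and it limits the point to a mismatch of named tests. It does not remove it: if the unpaired tests were meant only for between-group work, the paragraph names no rank test and no explicit matched test for the contrast it opens with. A condensed article may leave the mapping of tests to outcomes to a fuller plan, but naming unsuitable tests is a stated choice, not an omission.

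A second objection is that the models deal with the repeated measures. They can: xtlogit and xtgee with exchangeable correlation handle two visits per woman if the woman is the panel unit, and count outcomes are to be treated as Poisson. A reader might infer that p-values will be wrong for every non-normal and binary outcome. The article does not support that; at most the unadjusted step is affected.

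A reader might also infer that the faulty p-values decide which covariates enter the models. They do not. A comparison of visit 1 with visit 2 selects no covariate; screening relates covariates to outcomes, a different contrast.

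Finally, signed-rank and McNemar's test treat women as independent, whereas the Analysis section says that clustering within sites must be considered. This is true, and it is a reason not to rest effectiveness on any bivariate test.

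**Conclusion.** The point holds for the unadjusted baseline to 6-month comparisons. Used there in their standard forms, rank-sum and chi-square do not suit the paired data. With positive within-woman correlation the comparison of visits as two samples is conservative: a true error rate of about 0.1% to 2.7% for correlations from 0.3 to 0.7, and roughly 17 points of power lost at 0.5. Both results rest on assumed correlations, and the power figures on assumed effects as well; the loss is smaller at 0.3, larger at 0.7, and absent at zero.

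A reader might apply the large-sample formula to power, where 80% falls to Φ(2.80 − 1.96 × 1.41) ≈ 51% at correlation 0.5. That 29-point loss is for a normal-theory test on means and overstates what the simulated tests show. Nor would ignoring the pairing in this way produce a spurious finding of effectiveness, since it adds no false positives. Chi-square on the baseline-by-follow-up table is a separate matter: its p-value does not address change and should not be read as if it did.

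Because the error is conservative and confined to a preliminary step ahead of models that can handle repeated measures, severity is moderate and it is not a must-fix item.

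**What to change.** In the effectiveness paragraph of the Analysis section, name the tests by contrast:

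- Baseline against 6 months in the same women: paired t-test, Wilcoxon signed-rank for skewed or ordinal outcomes, McNemar's test for binary outcomes, and Stuart-Maxwell for more than two categories.
- Between groups of women (clinic against rehab, covariate screening): rank-sum and chi-square.

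Apply the same wording to the ART and substance abuse treatment outcomes, which follow a similar approach. Add that effectiveness conclusions rest on models that account for repeated measures within woman and for clustering within site, with the bivariate tests as unadjusted support.

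The cost is a sentence or two of text. No new data, visits or participants are needed.

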To measure the implementation processes and outcomes, we will undertake quantitative data collection with providers and review implementation records to assess fidelity of program implementation. Fidelity checks on a random basis will be conducted on the actual groups conducted. Clinic interventionists and other clinic staff who interact with patients participate in the pre-, mid-, and post-implementation FGDs and also complete the self-administered pre- and post-clinic surveys. We will assess seven implementation outcomes to determine program success, as proposed by Proctor and colleagues [13]. Not all implementation outcomes will be assessed across each of the four cycles; however, the protocol for measuring implementation outcomes will remain constant at each cycle. Some of the intervention outcomes will be measured quantitatively and others will be measured qualitatively. The standard implementation outcomes and their measurement methods are outlined in Table 1.

**Table 1 Tab1:** Standard implementation outcomes and their measurement methods

Implementation outcome	Description	Measurement	Data source	Time point
Appropriateness	The extent to which the WHC^a^ is congruent with the culture of the clinic setting	Focus group discussions	Clinic staff, community women, administrators	Formative
	Organizational Readiness	Texas Christian University organizational readiness for change [46]	Interventionists and administrators	Pre-implementation
	Comprehensive Services Linkage Referrals	Self-report	Participants of the WHC	6-month follow-up
	Comprehensive Services Linkage Referrals	Research staff report	Clinic and research staff	Daily
Acceptability	Feedback on the modified WHC	Focus group discussions	Clinic staff and administrators	Multiple time points from mid- to post-implementation
	Client satisfaction	The Client Satisfaction Questionnaire (CSQ-8) [47]	Participants of the WHC	6-month follow-up
Adoption	Current state of implementation of the WHC and challenges to implementing the WHC	Focus group discussions	Clinic staff	Mid- and post-implementation
Cost	Costs associated with implementing the WHC	Clinic-Patient Contact form [48]	Clinic staff	Throughout the implementation cycle
Feasibility	Exposure to and retention of the WHC	Number of WHC modules being delivered	Clinic staff	Throughout the implementation cycle

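### Patient satisfaction, measured only after the intervention at 6 months, is named as a leading covariate in the pre-post effectiveness model, where it controls no confounding and, depending on an unstated coding, can distort the effect or make it inestimable

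*Protocol article*

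**What the plan says.** The article describes a single-group contrast over time. Under Patient-level process and data collection, clinic staff "offer the adapted intervention to all women enrolled", and at 6 months "we will assess effectiveness of the program using pre-post comparisons". The Analysis section repeats the target: "To assess effectiveness, the analysis will compare changes from baseline to 6-month follow-up on the amount of alcohol consumption" and on further outcomes. For the multivariable step, "the xtlogit and xtgee function will be used to specify random effects or fixed effects", with an exchangeable correlation matrix. In the same paragraph, directly after saying that the models control for covariates, it adds: "One of the most important covariates in the model will be measures of patient satisfaction".

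The paragraph on receiving and adhering to ART lists as variables considered for the model patient characteristics and "measures of patient success with the WHC, patient satisfaction, and clinic-level characteristics (e.g., type of clinic, provider satisfaction".

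Table 1 shows when satisfaction is measured: "The Client Satisfaction Questionnaire (CSQ-8) [47] Participants of the WHC 6-month follow-up". The same table treats it as an outcome (acceptability), and the Analysis section makes it one of three groups of patient-level results, to be analysed mainly descriptively.

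**The concern.** All enrolled women are offered the WHC, so the visit indicator (6 months against baseline) carries the effect. Satisfaction with the programme cannot exist before the programme. It is a result of exposure, recorded at the same visit as the outcome. A variable that comes after exposure cannot be a confounder of that exposure, so there is no bias for this adjustment to remove.

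There is also a practical problem. A repeated-measures model has two rows per woman, and the score has a value for only one of them. Something must be put in the baseline row, or the row is lost. The article does not say which, nor whether the score is centred or interacted with visit. At stake is the meaning of the adjusted visit coefficient: it may no longer be the average change that the article says it will estimate.

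**Working it through.** The plan states no figure on this point, so there is none to reproduce. The check asks what happens to the visit coefficient under each plausible coding.

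**Inputs from the article.** 480 women enrolled and 90% expected follow-up give 480 × 0.90 = 432 baseline/6-month pairs. The correlation is exchangeable. The score exists at 6 months only.

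**Assumed inputs.** Score mean 24, SD 4, range 8 to 32; true change δ = -5 or 0; the 6-month outcome falls by β = 0, 0.25 or 0.5 per satisfaction point. None of these is in the article.

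**Model.** Y0 = α + e0 and Y1 = α + δ - β(S - 24) + e1, where the errors within a woman are correlated. The average change is δ.

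**Algebra by coding.**

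1. *Baseline score left missing, complete cases.* All 432 baseline rows go. The visit indicator is constant and its coefficient cannot be estimated.
2. *0 at baseline, raw score at follow-up.* Rewriting, Y1 = α + (δ + 24β) - βS. The visit coefficient becomes δ + 24β, the change extrapolated to a score of zero, which is outside the scale.
   - δ = -5, β = 0.25: -5 + 6 = +1
   - δ = -5, β = 0.5: -5 + 12 = +7
   - δ = 0, β = 0.5: 0 + 12 = +12
3. *0 at baseline, centred score at follow-up.* The visit coefficient is δ.
4. *6-month score copied to both rows.* Each woman has one row at each visit, so the score is uncorrelated with visit and the coefficient is δ. In a person fixed-effects model the score is constant within a woman and drops out.

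**Simulation** (432 pairs, 300 repetitions, generalised least squares with exchangeable correlation and robust SE). Mean visit coefficient, with SE:

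| True δ, β | No satisfaction | Copied to both rows | 0 then raw | 0 then centred | Baseline imputed |
|---|---|---|---|---|---|
| -5, 0 | -4.98 (0.34) | -4.98 (0.34) | -4.97 (1.82) | -4.98 (0.34) | -4.97 (0.34) |
| -5, 0.25 | -4.95 (0.34) | -4.95 (0.34) | +0.89 (1.82) | -4.95 (0.34) | -4.87 (0.34) |
| -5, 0.5 | -4.97 (0.35) | -4.97 (0.35) | +7.20 (1.84) | -4.97 (0.34) | -4.66 (0.34) |
| 0, 0.5 | 0.02 (0.35) | 0.02 (0.35) | +11.93 (1.82) | 0.02 (0.34) | 0.01 (0.34) |

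The raw coding agrees with the algebra to within simulation error. Even with no association (β = 0), its SE is 1.82/0.34 = 5.4 times larger. Imputed baseline scores (one stochastic draw, not full multiple imputation) attenuate the effect by (4.97 - 4.66)/4.97 = 6% at β = 0.5.

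**Logistic case.** The article names xtlogit and xtgee. In a small logistic GEE run (25 repetitions, same assumed score, 0.1 log-odds per point), the raw coding moved the visit log-odds ratio from about +0.5 to about -1.6, and a true null to about -1.9. With no association the SE rose from 0.13 to 0.63. Centred and copied scores left the estimate nearly unchanged.

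**The case against.** The strongest defence has four parts.

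- *Coding belongs in a full analysis plan, and harmless codings exist.* Both are true. A reader might infer that any use of satisfaction in a two-row model ruins the estimate. The table shows otherwise: copied or centred scores leave the linear visit effect unchanged, and a covariate that drops out of a fixed-effects model does no damage. But the article does not simply omit a detail. It chooses a post-exposure variable as a leading control, and no coding turns that variable into a confounder.
- *The effectiveness result does not rest on this model alone.* This stands. Descriptive results and paired tests come first, without satisfaction, and the adjusted visit coefficient is not named as the primary effect. The planned elimination of variables by likelihood ratio, AIC and BIC is weaker protection: it tends to keep satisfaction when it predicts the outcome, which is when raw coding biases the visit effect most.
- *Satisfaction may be meant as a predictor of change.* That is a fair exploratory question. The text, however, places it among the controls of the effectiveness model.
- *The ART list is only a set of candidates.* This stands, and it softens that part of the point.

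A reader might also be tempted by three further claims that the article does not support. The 10% expected to be lost (48 of 480) lack the 6-month outcome as well, so satisfaction does not cause that loss. Provider satisfaction need not share the defect: its timing is not stated, and staff are surveyed before and after implementation. Nor does Table 1 say that women who did not attend sessions are left out of the CSQ-8.

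**Conclusion.** The point holds in conditional form. The article names a post-intervention measure as a leading covariate for a pre-post effect and states no coding that would make it harmless. The visit effect can become inestimable (complete cases), be reversed or very imprecise (raw score with 0 at baseline), or be slightly attenuated (imputed baseline scores). It is essentially unchanged with a centred or person-constant score, but then the covariate controls no confounding. So no coding gives it a sound role as a control in this model.

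The sizes rest on an assumed score distribution, assumed slopes and mainly a linear model. They show what can happen and do not predict the trial's result. Variance inflation factors worked out for the raw-zero coding with independent rows would not describe the planned correlated-data models in general.

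The same reasoning covers the measures of patient success listed for the ART model if they are defined after exposure. The article does not define them.

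**What to change.** In the Analysis section:

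1. Remove patient satisfaction, and patient success where it is defined after exposure, from the models that estimate the pre-post effectiveness and ART effects.
2. State that these models adjust only for variables fixed before the WHC: site, site type and baseline characteristics.
3. Report the association of satisfaction or success with change as a separate analysis among women with follow-up, labelled exploratory and non-causal.

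In the simulation, leaving satisfaction out recovers the effect: -4.97 (SE 0.35) for a true -5, and 0.02 (SE 0.35) for a true 0. The cost is one paragraph of text. No new data are needed, and the descriptive satisfaction analysis stays as planned.
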